**Methods/design:**

A 24-week cluster randomized, double-blind, placebo-controlled study will be conducted on 104 adults ≥70 years. Nursing homes will be randomized to either of four groups: Ex-HMB (exercise intervention with HMB), Ex-Plac (exercise intervention with placebo), NoEx-HMB (no exercise intervention with HMB), and Controls (No exercise and no HMB). Intervention groups which include exercise will complete the individualized multicomponent (strength, balance and cardiovascular exercises) training program VIVIFRAIL. Intervention groups which include HMB supplementation will receive a 3 g/daily dose of free acid HMB in powder form. The primary outcome measure is the functional capacity. Secondary outcome measures are muscle strength and power, frailty and fall risk, body composition, biochemical analyses and cardiometabolic risk factor, disability and comorbidity, cognitive function and depression.

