## Methods/design

### Study design and settings

This is a cluster randomized, placebo-controlled study with four parallel groups. The study has been designed to determine the efficacy of HMB supplementation in addition to 24-weeks of multicomponent exercise and resistance training (the VIVIFRAIL program) in adults ≥70 years. Flowchart of the trial is shown in Fig. 1. Enrollment, intervention allocation, follow-up, and data analysis will be conducted according to the SPIRIT (Standard Protocol Items: Recommendations for Interventional Trials) statement [39, 40].

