### Randomization and blinding

After recruitment and baseline measurements, nursing home will be randomized to either of the four groups in clusters, according to a computer-generated sequence using the Sealed Envelope Ltd. online system. The cluster design is chosen to prevent influences on participants’ behaviours within a given nursing home unit. A stratified randomization will be used according to their initial functional status (A, B, C or D, see Fig. 2) to reduce imbalance between groups. The allocation will be concealed in a password protected computer file. Given the nature of the treatment (i.e., daily exercise and dietary supplementation program), participants will be aware of their group allocation. Outcome assessors and data analysts will be blinded to the treatment group assignment. Assessors will not be involved in intervention activities. A dedicated protocol will be defined to protect the confidentiality of data.

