### Interventions

#### Dietary supplementation

Intervention groups including HMB supplementation (Ex-HMB and NoEx-HMB) will receive a 3 g daily dose of free acid HMB in powder form (myprotein.co.uk, Cheadle, Cheshire, UK) dissolved freely into 250 mL of water during a 24-week intervention [34, 43]. Nursing staff will supply the doses as a part of their daily diet routine. Ex-Plac and Control groups will receive stevioside. Supplements will be packaged in indistinguishable envelopes and boxes, with an identification code for each participant and group. The compliance of supplementation will be monitored and ensured by medical staff working at the nursing home. Oral supplement and Vitamin D will be provided to maintain an acceptable nutritional status.

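### The protocol contradicts itself on whether participants are blinded to HMB versus placebo: the abstract and packaging imply they are, the blinding section says they are not

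*Protocol article*

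**What the plan says.** Three places in the protocol article bear on participant blinding.

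- **Abstract, Methods/design:** "A 24-week cluster randomized, double-blind, placebo-controlled study will be conducted on 104 adults ≥70 years".
- **Randomization and blinding:** "participants will be aware of their group allocation". The reason offered is introduced with "Given the nature of the treatment (i.e., daily exercise and dietary supplementation program", so it covers the supplement as well as the exercise. The section then adds: "Outcome assessors and data analysts will be blinded to the treatment group assignment". It names no other blinded party.
- **Dietary supplementation:** "Ex-Plac and Control groups will receive stevioside", and "Supplements will be packaged in indistinguishable envelopes and boxes, with an identification code for each participant and group".

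The main text describes the design without the blinding label: "This is a cluster randomized, placebo-controlled study with four parallel groups" (Study design and settings). The Discussion also calls the trial randomized and placebo-controlled only. The double-blind claim therefore appears once, in the abstract.

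**The concern.** Exercise cannot be hidden from the people who do it. A powder supplement can in principle be hidden, and that is the usual reason for giving a placebo to both non-HMB groups. The trial's stated aim is the efficacy of HMB on top of the exercise programme, so Ex-HMB vs Ex-Plac is a central comparison and one that a placebo could protect.

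The primary outcome is the SPPB: balance, gait speed and five sit-to-stands, all performed by the participant. Among the secondary outcomes, the 1RM tests, grip strength and sit-to-stand power depend on effort, and the depression scale and SARC-F rest on participants' answers. Blinded assessors limit bias in how these are scored. They do not limit how hard a participant tries, or what a participant reports, when the participant knows which product was given.

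Two things are at stake: whether the HMB comparisons are protected from expectation effects, and whether readers are told correctly who was blinded to what.

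**Working it through.** The document gives no figure for this point, so the check is a comparison of texts.

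**Step 1. What knowing the group means.** The four groups are defined by two factors.

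| Group | Exercise | Supplement |
|---|---|---|
| Ex-HMB | yes | HMB |
| Ex-Plac | yes | stevioside |
| NoEx-HMB | no | HMB |
| Control | no | stevioside |

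A participant who knows the group knows both factors. The awareness statement is not limited to exercise, and its stated reason names the supplement. Taken literally, it unblinds participants to HMB versus stevioside.

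**Step 2. Which comparisons depend on this.** Four groups give 4 × 3 / 2 = 6 pairwise comparisons.

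- Two differ in supplement only: Ex-HMB vs Ex-Plac and NoEx-HMB vs Control. Participant masking is possible in principle, and these two are damaged if it is absent.
- Two differ in exercise only: Ex-HMB vs NoEx-HMB and Ex-Plac vs Control. Participants know their exercise assignment under any reading.
- Two differ in both: Ex-HMB vs Control and Ex-Plac vs NoEx-HMB. The exercise part is open in any case.

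**Step 3. Try each reading that might reconcile the texts.**

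| Reading | Abstract label | Blinding section | Indistinguishable packs |
|---|---|---|---|
| A. Participants know both exercise and supplement | untrue in its ordinary sense | correct | do not serve to mask participants |
| B. Participants know exercise only | true for the supplement, not for exercise | wrong: it names the supplement and does not limit the awareness | consistent |
| C. Double-blind means assessors and analysts | defensible, but needs to be said | correct | unexplained as far as participants are concerned |

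No reading leaves all three places correct and clear as they stand. A and C leave the two supplement-only comparisons open to participants. B protects them, but only if the blinding section is rewritten.

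**Step 4. Size.** The document has no estimate of an expectation effect on the SPPB and nothing from which to derive one. The Sample size section gives a target difference of 2 points with a standard deviation of 3. Neither says how much of a difference knowledge of the supplement could produce.

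**The case against.** The best case for the plan is that awareness was meant for the exercise assignment and the sentence is loosely worded. The operational section supports this: a placebo is specified for both non-HMB groups and the packs are made to look alike. The label may also be no more than an error in the abstract, since neither the design section nor the Discussion repeats it. In addition, assessors and analysts are blinded and assessors take no part in the intervention, so bias in scoring is already limited.

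Much of this stands, and it rules out several stronger conclusions that a reader might draw.

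- *That the placebo has lost its purpose.* This follows only if the blinding section is carried out as written. Under reading B the placebo does its job, and the document does not settle which reading is meant.
- *That the pack code unblinds the trial.* The text says that codes exist for participant and group. It does not say that a code reveals the product, or what staff are told.
- *That participant-level codes would cure the problem.* Homes are randomised as clusters, so residents of a home share one product. One disclosure unblinds that home whatever the code looks like. Codes that do not identify the group could at most limit spread to other homes.
- *That nursing staff and carers are blinded.* No section says so. The article describes matched packs and does not say whether the dissolved drinks match in taste or appearance.
- *That the bias amounts to a given number of SPPB points.* Nothing in the document supports a figure.

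The contradiction itself is not answered. The blinding section names the supplement in its reason, and a fuller protocol or analysis plan that supplied more detail would not make the published statements agree.

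**Conclusion.** The point holds as an internal contradiction on a stated design property. The abstract and the supplement packaging imply that participants are masked to HMB versus stevioside. The blinding section says that they know their group, gives the supplement as part of the reason, and lists only assessors and analysts as blinded.

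The consequence is conditional. If the blinding section is followed as written, the two supplement-only comparisons on the SPPB, and on the effort-based and self-reported secondary outcomes, combine expectation with any HMB effect, and the double-blind label is untrue. If awareness was meant for exercise only, the comparisons are protected and the fault is one of wording. The size of any bias cannot be derived from the document.

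This rests on two assumptions: double-blind carries its ordinary sense of including participants, and participant effort or expectation can affect performance tests and self-report. It should be corrected, because as the text stands a reader cannot tell whether the central HMB comparison is blinded to participants.

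**What to change.** 1. In Randomization and blinding, limit participant awareness to the exercise assignment, and state that participants are not told whether they receive HMB or stevioside, as the packaging implies.
2. In the same section, state separately for exercise and for supplement whether participants, nursing staff, outcome assessors and data analysts are blinded. Claim blinding only for those to whom it truly applies.
3. In the abstract, replace the double-blind label with wording that matches, such as blinded for supplement and assessor-blinded for exercise.
4. If participants will in fact know their supplement, drop the double-blind label instead and describe the HMB contrasts as open to participants.

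Optional: use pack codes that do not identify the group. This limits spread of unblinding between homes, not within a home.

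Items 1 to 4 cost a few sentences, plus adherence to whichever rule is stated. The optional item means a change to the coding list, and relabelling if packs have already been prepared; the Discussion planned baseline assessment for March 2019.

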**Fig. 2 Fig2:**
[figure not shown]
Summary of the VIVIFRAIL multicomponent exercise intervention program. Individualization based on baseline testing scores. Full guidelines: www.vivifrail.com

### Interventions

#### Dietary supplementation

Intervention groups including HMB supplementation (Ex-HMB and NoEx-HMB) will receive a 3 g daily dose of free acid HMB in powder form (myprotein.co.uk, Cheadle, Cheshire, UK) dissolved freely into 250 mL of water during a 24-week intervention [34, 43]. Nursing staff will supply the doses as a part of their daily diet routine. Ex-Plac and Control groups will receive stevioside. Supplements will be packaged in indistinguishable envelopes and boxes, with an identification code for each participant and group. The compliance of supplementation will be monitored and ensured by medical staff working at the nursing home. Oral supplement and Vitamin D will be provided to maintain an acceptable nutritional status.

#### Multicomponent physical exercise program

Intervention groups including exercise (Ex-HMB and Ex-Plac) will complete an individualized multicomponent training program, VIVIFRAIL [16], 5 days a week during 24 weeks. Free on-line resources and program guidelines are available online (http://www.vivifrail.com/resources). The VIVIFRAIL program has been carefully designed for people ≥70 years and includes six programs or “Passports” adapted for each participant’s condition according to their functional limitation (serious [A], moderate [B], slight [C] and no limitation [D]) and risk of falling (B+ and C+). Individualization is made based on the baseline testing scores (i.e., the VIVIFRAIL test). Each program combines strength, power, balance, walking, stretching and cardiovascular exercises, in the named “VIVIFRAIL Wheel”. Training sessions are daily and weekly organized (type of exercise, steps and reps) in individual “Passports”. A summary of the exercise program is shown in Fig. 2.

The VIVIFRAIL program has a free mobile app available on iOS and Android, the latest version of which, (launched in January, 2019) allows the recording of the results of the test to automatically assign each participant to a training program. The App includes a calendar with a daily progression, training monitoring and rate of perceiving effort assessment.

### Outcome measures

*Functional capacity (primary outcome):* The Short Physical Performance Battery (SPPB) [42] scores from 1 (low mobility) and 12 (full mobility) points based on three tests: balance tests (tandem, semi-tandem and one foot next to the other), gait speed and 5-sit-to-stand test. The SPPB has been extensively administrated in older adults [17, 44]. The resulting scores are part of the VIVIFRAIL test to determine each individual’s physical exercise program [16].

*Maximal muscle strength and power output:* grip strength measurement (Jamar digital dynamometer, NexGen ergonomics, Pointe Claire, Quebec, Canada) [45], one repetition maximum (1RM) seated leg press and vertical bench press strength (Salter Ltd., Barcelona, Spain) and muscle power (T-Force Dynamic Measurement System, Ergotech Consulting SL, Murcia, Spain) [46, 47], sit-to-stand muscle power [48], in the same order with a 3-min rest between tests in order to diminish fatigue [49].

*Frailty and fall risk*: frailty phenotype determination [50], complete falls history and fall risk assessment, physical examination [16].

*Body composition:* Body composition will be assessed using dual-energy x-ray absorptiometry - DXA (Hologic, Bedford, MA; Discovery A), between 6:00 AM and 9:00 AM after a ≥ 10-h fast and after participants had voided their bladders [51].

*Blood pressure and resting heart rate:* Systolic and diastolic blood pressure, as well as resting heart rate will be measured after 10 min of rest, two times 2 min apart (M6 upper arm blood pressure monitor Omron. Omron Health Care Europe B.V. Hoofddorp, The Netherlands).

*Haematology*: Erythrocyte count, haematocrit, haemoglobin, platelets, leukocytes and erythrocyte mean corpuscular volume will be quantified by Coulter Cell Counter.

*Biochemical analyses*: glucose, high-density lipoprotein (HDL), total cholesterol (TC), triglycerides (TG), glycosylated haemoglobin (HbA_1c_), thyroid-stimulating hormone (TSH), C-reactive protein (CRP), albumin, prealbumine, transferrin, insulin-like growth factors (IGF-1 and IGFBP-3), creatine phosphokinase (CPK) and 25-hydroxyvitamin D (25[OH]D). Blood analysis will be conducted with standard methods using an autoanalyzer. Insulin sensitivity will be derived from the homeostatic model assessment for insulin resistance (HOMA-IR).

*Nutritional status:* The Mini-Nutritional Assessment (MNA-SF) [52] will be used to evaluate nutrition status and malnutrition risk.

*Sarcopenia*: The SARC-F will be used to diagnose sarcopenia [53].

*Disability and comorbidity:* Barthel index [54] and Lawton index [55] will be used to assess disability in basic activities and instrumental activities of daily living, respectively. Given the limitations of comorbidity indexes in older people [56], we will consider comorbidity when a participant presents two or more geriatric syndromes from a list of selected geriatric syndromes, as previously proposed [57].

*Cognitive function and depression:* the validated Spanish version of the Mini-Mental State Examination (MMSE) [58] will be used to assess cognitive function. Depression will be assess with the Spanish version of the 15-item Yeasavage geriatric depression scale [59].

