## Background

To date, people are living more years than ever before in history and the world’s aging is rising at a staggering rate [1]. Thus, strategies focused on health maintenance for aging people through exercise and proper nutrition are required to contribute to lifelong wellbeing and prevent ageing diseases and chronic illness. Frailty, sarcopenia, dynapenia and sarcopenic obesity states are the main metabolic complications in older people and represent a major public health challenge [2–4]. A recent estimation from the Eurostat online database (28 European countries) suggests increments from 60 to 70% of individuals with sarcopenia in 2045 affecting 12.9 to 22.3% of people over 65 years old [5]. These diseases are caused by a degenerative loss of muscle mass (muscle wasting), strength and mobility. The combination of exercise with protein dietary supplementation is proven to be highly effective to increase muscle mass and strength in older adults [6–8].

Evidence states that exercise in older people is a main component in frailty prevention (increases strength and decreases falls incidence) and functional capacity preservation (increases mobility and autonomy) [8–10]. In turn, weak elders have greater risk of disability, hospitalization, morbidity and death [3, 11]. In addition to a better physical condition, exercise has a clear impact on psychological well-being in older people [12]. Although much remains to be done, the possibility of physical exercise as the new medication for the twenty-first century is truly inspiring. The first step of this revolution is that the question is turning from “may I prescribe physical activity for older people?” to “what kind of exercise must I prescribe?” [13]. Reducing sedentary behaviours and promoting exercise training in older adults living in nursing homes stands as a main global challenge [14, 15].

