Very recently, the ERAMUS+ co-funding VIVIFRAIL project (http://www.vivifrail.com) has developed a multicomponent exercise program (strength, balance and cardiovascular exercises), carefully adapted, for improving functional capacity for older people above 70 years [16]. The program includes a practical guide for testing and prescribing the physical training according to each specific condition (serious, moderate, slight or no limitation, and with or without risk of falling). Furthermore, the VIVIFRAIL App allows individuals’ monitoring and provides clear instructions to effectively complete the program within the everyday environment. Now that long-term exercise interventions in older adults are more possible than ever [17], what is now required is to examine the effectiveness of this program on relevant health and functional outcomes for older adults and nursing homes residents [15].

The β-hydroxy-β-methylbutyrate (HMB) dietary is a bioactive metabolite formed from the decomposition of leucine, an essential branched-chain amino acid. The importance of leucine has anti-catabolic properties and plays an important role in protein metabolism, glucose homeostasis, insulin action and recovery from exercise [18–20]. A dose of 3 g of HMB dietary supplementation provides 60 g of leucine, which otherwise would imply 600 g of high biological value protein [21]. The HMB supplementation is affordable (around 50€/kg) and its consumption is safe with no adverse effects [22, 23]. In older adults > 60 years old, HMB is demonstrated to have anti-catabolic effect, enhance protein synthesis, attenuate proteolysis, increase muscle mass and decrease muscle damage [24–26]. Despite the fact that HMB efficacy varies [25], a meta-analysis concluded that HMB supplements contribute to the preservation of muscle mass in old age [27]. Based on these findings, the supplementation of HMB appears to be an effective strategy to prevent metabolic and physical complications in ageing (frailty, dynapenia, sarcopenia and sarcopenic obesity) and preserve health, functional capacity and strength in older people.

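### Sarcopenia is to be diagnosed by SARC-F alone, so measured muscle mass plays no part in that outcome, although DXA, grip strength and gait speed are already collected at baseline and week 25

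*Protocol article*

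**What the plan says.** The definition of the sarcopenia outcome is one sentence under Outcome measures: "The SARC-F will be used to diagnose sarcopenia". A reference is cited, but no cut-off, item or further criterion is given. Table 2 schedules sarcopenia at baseline, week 12 and week 25.

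The Background lists frailty, sarcopenia, dynapenia and sarcopenic obesity together and then says: "These diseases are caused by a degenerative loss of muscle mass (muscle wasting), strength and mobility". It also gives the case for the supplement, stating that "a meta-analysis concluded that HMB supplements contribute to the preservation of muscle mass in old age".

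Outcome measures names a measurement for each of those three elements:

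- Muscle mass: "Body composition will be assessed using dual-energy x-ray absorptiometry - DXA". The protocol does not list which DXA outputs will be reported.
- Strength: "grip strength measurement" with a digital dynamometer.
- Mobility: "gait speed and 5-sit-to-stand test", both parts of the SPPB.

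The Abstract lists body composition as a secondary outcome in its own right. It does not name sarcopenia in that list.

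**The concern.** The protocol describes sarcopenia partly in terms of muscle mass, measures body composition by an instrument suited to that purpose, and then settles the diagnosis with a different instrument alone.

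This matters more here than in many trials because of the rationale for HMB. The Background treats preservation of muscle mass in old age as the clear effect of the supplement and calls the evidence on strength and functional performance contradictory. The same section names sarcopenia among the conditions that HMB might prevent. An outcome called sarcopenia that contains no measured muscle mass leaves out the element on which the authors consider HMB best supported.

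Interpretation is then awkward either way. A null result on sarcopenia could mean that HMB has no effect on it, or only that mass was not part of the classification. A positive result would carry the name of a muscle disease without a muscle measurement behind it.

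**Working it through.** The point concerns how an outcome is defined, and the plan gives no figure for it, so there is nothing to reproduce. The check sets the outcome definitions beside the schedule in Table 2.

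| Element named in the Background | Measurement in Outcome measures | Baseline | Week 12 | Week 25 | Part of the stated sarcopenia diagnosis? |
|---|---|---|---|---|---|
| Muscle mass | DXA body composition | yes | no | yes | no |
| Strength | Grip strength | yes | yes | yes | no |
| Mobility | Gait speed within SPPB | yes | yes | yes | no |
| Sarcopenia outcome | SARC-F | yes | yes | yes | sole instrument |

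1. **Does DXA enter the diagnosis at week 12?** It cannot enter from that visit, because sarcopenia is scheduled then and DXA is not. This follows from Table 2 alone and needs no knowledge of what SARC-F contains.

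2. **Does DXA enter at baseline or week 25?** The rule is the same single sentence for all visits, and nothing in Outcome measures or Table 2 adds a DXA criterion at the other two. As stated, no sarcopenia classification uses measured muscle mass.

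3. **Is this an omission that a fuller document would fill?** No. The article names the instrument and calls its use diagnosis, so the point is about a rule that is stated. Cut-offs and scoring could well sit elsewhere, and their absence is not part of the point.

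4. **Are the ingredients for a measured classification available?** Yes, at baseline and week 25, where DXA, grip strength and SPPB are all ticked. At week 12 grip strength and SPPB are available but DXA is not.

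5. **How many classifications are affected?** Under the stated rule, all of them. The recruitment target under Sample size is 104 residents (4 groups × 26). That is the upper limit per visit. If the full 30% loss to follow-up that the protocol allows for occurred, about 104 × 0.70 = 72.8, or 73 residents, would remain at the end. These figures count classifications made without measured mass. They are not counts of wrong classifications.

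**The case against.** The strongest reply has four parts.

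**The instrument's content is not in the document.** The protocol does not describe SARC-F's items, scoring or purpose. That it is a short symptom questionnaire used for screening is general knowledge. This stands as a limit: a reader might infer that SARC-F is invalid as a diagnosis or will misclassify residents at some rate, and the document gives no accuracy figure to support that. The narrower point survives, because the absence of measured muscle mass follows from the stated rule and Table 2.

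**The Background sentence is not a case definition.** It is a remark on the causes of four conditions taken together, and a statement of cause does not oblige the diagnosis to measure each cause. This also stands. The sentence shows what the authors understand sarcopenia to involve. It does not make the SARC-F rule a formal contradiction.

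**Muscle mass is assessed elsewhere.** A reader might infer that the trial cannot show the muscle-mass effect expected of HMB. The documents do not support that: DXA body composition is a separate secondary outcome at baseline and week 25, and strength and gait are also measured in their own right. The primary outcome is SPPB, and neither it nor the sample size depends on SARC-F. Nor is SARC-F bound to stay unchanged under treatment, since it might respond indirectly if function improves.

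**One instrument at all three visits is a coherent choice, and a derived DXA variable might be planned elsewhere.** The first part is fair, and the remedy gives up the week-12 classification. The second part is possible, but the article as written assigns the diagnosis to SARC-F, so the sentence would still need to change.

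**Conclusion.** The point holds for the sarcopenia outcome only, and it is minor. As written, sarcopenia is diagnosed at all three visits without measured muscle mass, although the protocol associates the condition with loss of mass, strength and mobility and measures all three at baseline and week 25. A treatment effect reported as an effect on sarcopenia would not directly reflect muscle mass.

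The size of any misclassification cannot be derived from the document, and none is claimed. The primary analysis, power and the separate DXA outcome are untouched.

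The conclusion rests on reading the single sentence under Outcome measures as the whole rule, which the week-12 schedule supports. The remedy rests on one further assumption: that lean mass is among the DXA outputs, since the protocol says only body composition.

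**What to change.** Replace the sentence on sarcopenia under Outcome measures so that it does two things:

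- At baseline and week 25, classify sarcopenia from DXA lean mass, grip strength and gait speed, using one published definition. Name the definition and fix its cut-offs before the data are analysed, so that no choice among definitions is made with results in view.
- At baseline, week 12 and week 25, report SARC-F as a questionnaire score and do not call it the diagnosis.

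Amend the sarcopenia row of Table 2 to match, and state that lean mass will be taken from the DXA scan.

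The cost is a reworded sentence, a table edit and one derived variable. No new visit, test or burden on residents is needed. The downside is that there is no sarcopenia classification at week 12, only the SARC-F score.
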